#### Health Care Costs

Health care cost to the Ministries of Health (ie, hospitalization, emergency room visits, and home care services) will be captured from administrative databases (from provincial and regional authority databases).

#### Older Adult Functional Status and Quality of Life

Older adults’ functional status, mood, well-being, and social supports will be assessed using the following:

Hospital Admission Risk Profile [28]Participant self-reported perception of safety and quality of care (researcher-developed)Mini-Mental State Examination [29]Satisfaction with RM (researcher-developed)Older People’s Quality of Life Questionnaire [30]

#### Family and Friend Caregiver Functional Status and Quality of Life

Measures include adapted versions of the following:

Selected Caregiver Assessment Measures [31]California Caregiver Resource Centers Uniform Assessment Tool [32]Zarit Burden Interview [33]Positive Aspects of Caring [34]Stanford Presenteeism Scale [35]Todtman Financial Impact Scale [36]Satisfaction with in-home monitoring assessment (researcher-developed)

#### Remote Monitoring Data

Sensor notifications are atypical events (eg, missed medication, lack of movement from the bed) of client’s activities of daily living that will trigger a message sent to a family/friend caregiver. Currently, all system (ie, client) activity is logged and viewable on a dashboard available to authorized individuals via computer or on a mobile device. As well, a history of the clients’ activity/nonactivity is logged (eg, fridge door opened, bathroom motion idle). The system has a search function such that client activity can be determined by sensor (eg, bed, medication) over several months to determine emerging and changing patterns. Patterns will be identified by the application of algorithms. Alternatively, all activity of a day can be viewed in chronological order to generate a description of the clients’ daily behavior patterns. The notification data has the potential to form a baseline of participant (client) behavior in the home, and trends or models of a participant’s usual activity or behavior can be established and then used to identify changes. Data collected from camera sensors will not be assessed.

### Data Analysis

#### Quantitative Data

Quantitative data will be analyzed at baseline, with subsequent analysis of primary/secondary outcomes at 6 months and 12 months. Using SPSS Statistics version 25 (IBM Corp) statistical software, descriptive statistics will provide a profile of study participants including demographics, current diagnoses, length of home care before the study, and model of care (RMHC versus usual care). The provisional effect of the intervention on the primary outcome will be tested using a prospective chi-square test of independence (continuity-corrected) between the experimental and control groups (Fisher exact test). Repeated measures analysis of variance will measure mean differences between groups on continuous variables. We intend to use multivariate survival analyses methods using a relevant time dependent outcome based on the ability to accurately track the main event of interest (ie, institutionalization) [24]. We will conduct within and between province analyses on secondary outcomes. Subgroup analyses will include examining differences based on sex (male/female) in both clients and family/friend caregivers.

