**Methods:**

The design for this study is an unblinded pragmatic randomized controlled trial (PRCT) with two parallel arms in two geographic strata (Ontario and Nova Scotia). Quantitative and qualitative methodologies will be used to address the study objectives. This PRCT is conceptually informed by the principles of client-centered care and viewing the family as the client and aims at providing supported self-management.

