### Sample Size Calculation

The sample size calculation is based on data from one health region included in the study to estimate the study’s main outcome (time to higher levels of care). The following criteria were used to estimate sample size: the total institutionalization proportion among controls being equal to 0.41 and the proportion or the experimental subjects at 0.27 (ie, a 34% reduction compared to controls); a 10% dropout and/or lost to follow-up rate; a power of 80% and a statistical significance level of alpha=.05. This resulted in an estimate of 160 participants for the intervention group and 320 for the control group for a total target study size of 480 participants across the study sites [25,26]. We opted to increase the study power by using a 2:1 ratio of controls to intervention subjects due to the cost of the intervention.

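### The only firmly specified test of the primary outcome is pooled, unadjusted and needlessly conservative; one prespecified, province-stratified and adjusted analysis would have at least as much power with data already collected

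*Protocol article*

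**What the plan says.** The protocol article (Data Analysis, Quantitative Data) tests the provisional effect on the primary outcome with a "chi-square test of independence (continuity-corrected) between the experimental and control groups (Fisher exact test" in brackets. No stratum and no covariate is mentioned. The same paragraph states an intention to use multivariate survival methods for institutionalization, subject to the event being tracked accurately. It names neither covariates nor strata for them, and does not say which analysis decides the primary question.

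The Methods part of the abstract describes "two parallel arms in two geographic strata (Ontario and Nova Scotia" as the design. In the analysis section, province appears in one sentence: "We will conduct within and between province analyses on secondary outcomes".

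Baseline data are collected before allocation (Recruitment). Age is on the demographic form (Phase I: Survey Data Collection). The "Hospital Admission Risk Profile" and the Mini-Mental State Examination are among the client measures, and standardized instruments are completed at each time point, baseline included.

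The Sample Size Calculation uses "the total institutionalization proportion among controls being equal to 0.41" and "the proportion or the experimental subjects at 0.27", with "a power of 80% and a statistical significance level of alpha=.05", 10% loss and two controls per intervention participant. It arrives at 160 + 320 = 480.

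**The concern.** Three features of the firm test sit badly with the rest of the design.

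- **Two tests for one comparison.** The corrected chi-square and Fisher's exact test are different procedures and can fall on opposite sides of 0.05. The sentence does not say which one decides.
- **An unnecessary correction.** With hundreds of participants per arm, the continuity correction mainly makes the test spend less than its nominal alpha.
- **Unused information.** Province and baseline risk are known for every participant before allocation, but the firm test uses neither. The 0.41 control rate comes from one health region, so the rate elsewhere is unknown, and a chance imbalance in province or baseline risk would go uncorrected.

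The analysis that could address the last two points is the one left conditional and undefined. What is at stake is efficiency and a clear decision rule. The validity of the test is not in doubt.

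**Working it through.** **Inputs.** From the Sample Size Calculation: p1 = 0.27 (intervention), p2 = 0.41 (control), difference d = 0.14, ratio r = 2, alpha 0.05, power 80%, loss 10%. Sidedness is not stated; two-sided is assumed. Evaluable numbers after 10% loss: 160 × 0.9 = 144 and 320 × 0.9 = 288.

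**1. Reproducing 480.** The pooled rate is (0.27 + 2 × 0.41)/3 = 0.3633. The uncorrected size of the intervention arm is

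n = [1.960 √(1.5 × 0.3633 × 0.6367) + 0.8416 √(0.27 × 0.73 + 0.41 × 0.59/2)]² / 0.14² = (1.1545 + 0.4746)² / 0.0196 = 135.4, so 136.

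The continuity-corrected size is

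n_c = (n/4) [1 + √(1 + 2(r + 1)/(n r d))]² = (135.4/4) [1 + √(1 + 6/(135.4 × 2 × 0.14))]² = 145.9, so 146.

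| Formula | Intervention arm | Total after dividing by 0.9 | Total after multiplying by 1.10 |
|---|---|---|---|
| Two-sided, uncorrected | 136 | 152 × 3 = 456 | 150 × 3 = 450 |
| Two-sided, corrected | 146 | 163 × 3 = 489 | 161 × 3 = 483 |
| One-sided, corrected | 117 | 130 × 3 = 390 | 129 × 3 = 387 |

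Only the two-sided corrected formula comes close to 480 (1.9% above it, or 0.6% with the other allowance for loss). The sample size and the corrected test therefore agree. The correction itself accounts for 489 − 456 = 33 participants.

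**2. Exact power and size.** Power is the sum, over all pairs (x, y) that the test rejects, of Bin(x; 144, 0.27) × Bin(y; 288, 0.41). With N = 432 and a, b, c, d here the cell counts, the uncorrected statistic is N(ad − bc)² divided by the product of the four margins. The corrected one replaces |ad − bc| by |ad − bc| − N/2. Size uses the same sum with a common rate.

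| Test | Power, 144/288 | Power, 160/320 | Size at 144/288, rate 0.363 | Size at 144/288, rate 0.41 |
|---|---|---|---|---|
| Corrected chi-square | 79.5% | 84.0% | 3.9% | 4.0% |
| Fisher exact | 81.1% | 85.9% | 4.4% | 4.6% |
| Uncorrected chi-square | 82.5% | 86.3% | 5.0% | 5.0% |

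At 144/288 the correction costs 82.5 − 79.5 = 3.0 points, and Fisher 82.5 − 81.1 = 1.4 points. The two named tests differ by 1.6 points in power, so they disagree on some tables that can arise.

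**3. Stratification and adjustment.** These were simulated for the event proportion at 144/288, with 4,000 trials per setting and marginal rates held at 0.41 and 0.27. Monte Carlo error is about √(0.83 × 0.17/4000) = 0.6 points. Assumptions: two provinces of equal size, allocation balanced within each, and one normally distributed baseline score. The province gap is a difference in log-odds. The AUC is that of score and province together, in controls.

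| Assumed score log-odds per SD | Assumed province gap | AUC | Uncorrected | Province-stratified (Cochran-Mantel-Haenszel) | Logistic, province + score |
|---|---|---|---|---|---|
| 0 | 0 | 0.50 | 83.2% | 83.3% | 83.2% |
| 0 | 0.5 | 0.56 | 83.4% | 83.7% | 83.4% |
| 0 | 1.0 | 0.62 | 83.6% | 84.8% | 84.7% |
| 0.5 | 0.5 | 0.65 | 82.8% | 83.1% | 84.8% |
| 1.0 | 0.5 | 0.75 | 82.7% | 82.9% | 88.9% |
| 1.5 | 0.5 | 0.82 | 82.9% | 83.2% | 92.9% |

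Stratification by province adds 0 to about 1 point over the uncorrected test. Adjustment adds nothing when the covariates carry no information, and about 2, 6 and 10 points in the last three rows (84.8 − 82.8, 88.9 − 82.7, 92.9 − 82.9). The log-rank and Cox analyses were not simulated.

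**The case against.** The best defence has five parts.

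- **The test is only provisional, and a multivariate survival analysis is intended.** This stands, so it would be wrong to infer that the plan's final primary analysis is definitely unadjusted. But the survival analysis is conditional, names no strata or covariates, and is not designated as primary. The sole firm commitment is the pooled test.
- **Covariate lists belong in the full protocol or the SAP.** Their absence from an article is not the point here. The article does state a particular test for the primary outcome and does name province analyses for secondary outcomes only. Those are stated choices.
- **The sample size was calculated for this test.** This stands. A reader might infer that the trial is underpowered. The arithmetic says otherwise: 79.5% against a planned 80%, from a test that is conservative but valid.
- **The gain from adjustment is assumed.** This also stands. The article gives no prognostic strength for the Hospital Admission Risk Profile or the Mini-Mental State Examination, so neither can be called a strong predictor, and the lower end of the range is zero. Nor does adjustment in a logistic or Cox model generally narrow the interval for the log odds or hazard ratio. Power rises because the conditional effect lies further from the null than the marginal one, so the adjusted ratio answers a slightly different question.
- **Geographic strata appear only in the abstract.** The Recruitment section describes blocks of three without saying that they are formed within province. An argument that the analysis must mirror stratified randomization is therefore not established. Matching the analysis to the declared strata remains sensible, though the power gained is small.

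**Conclusion.** The point holds as a missed efficiency gain together with an unsettled decision rule. It is not an error in the sample size or a threat to validity. Under a two-sided 0.05 level and 144/288 evaluable, the continuity correction costs about 3 points of power (79.5% against 82.5%) and leaves the true size near 3.9%. That part rests only on the article's planning figures and assumed sidedness. Province stratification adds 0 to about 1 point. Covariate adjustment adds 0 to about 10 points across assumed AUCs from 0.50 to 0.82, and in these simulations did not lose power beyond Monte Carlo error. The change is worth making, since it uses variables already collected.

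**What to change.** Before outcome data are examined, amend the Quantitative Data section as follows.

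1. Name one primary analysis: a log-rank test stratified by province, with a province-stratified Cox model for the effect estimate.
2. For the 12-month proportion, use a Cochran-Mantel-Haenszel test stratified by province, without continuity correction.
3. Adjust the effect estimate for a short list fixed now: baseline Hospital Admission Risk Profile, baseline Mini-Mental State Examination and age.
4. Delete the corrected chi-square and Fisher pair.
5. Because an adjusted odds or hazard ratio is a conditional effect, also report a marginal risk difference.

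The cost is a wording change and a slightly longer results table. No new data and no change in sample size are needed. The one real trade-off is the conditional reading of the adjusted ratio, which item 5 covers.

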## Methods

### Study Design

This 4-year study is an unblinded pragmatic randomized controlled trial (PRCT) with two parallel arms [19-22]. PRCTs are well-suited to supporting decisions about complex interventions tested in the real world when comparing with usual care [23,24]. The objective of the study is to examine the effectiveness of the RMHC versus usual home care in maintaining the client in their place of residence and delaying or preventing admission to higher levels of care such as hospitalization or long-term care.

This study builds on the findings of previous pilot studies conducted in the provinces of New Brunswick, Alberta, Nova Scotia, and British Columbia. The primary aims of this study are to test whether (1) RM along with usual home care (the intervention) versus usual home care alone (control) allow older adults with complex care needs to remain in their home longer and delay or avoid admission to higher levels of care (eg, hospitalization and long-term care), (2) intervention is cost effective, and (3) intervention will improve the quality of life for clients and family/friend caregivers. The primary outcome for this study is the occurrence of and time to events such as terminal admission to hospital awaiting admission to long-term care and direct admission to long-term care. The secondary outcomes for this study are (1) health care costs, (2) client functional status and quality of life in the home, (3) family/friend caregiver stress, and (4) family/friend caregiver functional health status.

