### Recruitment

Participant enrollment in the PRCT is supported by the respective provincial regional authority. Home care recipient participants will be assessed by the case coordinator or case manager in the regional authority against the inclusion and exclusion criteria (see Textbox 1).

Consent to participate in the study will be obtained at the first meeting with the researcher and the patient and family/friend caregiver. Once consent is obtained from the participants (client and their family/friend caregiver), research staff will collect baseline data before initiating random allocation into control and intervention groups. Using block randomization, participants will receive either usual home care or RM with usual home care [27]. Randomization will occur as follows:

Twelve ping pong balls will be placed in a containerFour of each of the ping pong balls will be numbered 1 to 3Each block of 3 participants will be numbered sequentially from 1 to 3 as they appear on the master recruitment listA ping pong ball will be pulled from a container and whatever number that ball is will correspond to the numbered participant; it is that participant who will receive the interventionThe remaining 2 participants will be in the control arm (no intervention)

Allocation bias will be addressed through allocation concealment; neither the case coordinator/case manager in the home care agency or research staff will know to which group the individual will be assigned a priori.

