#### Phase I: Survey Data Collection

Researchers will meet with clients and family/friend caregivers in the home of the client or by phone at baseline, 6 months, and 12 months to collect data. It is expected the interviews will last no more than one hour. Paper format questionnaires including standardized instruments and researcher-developed questions will be used to collect data at each time point (see Measures). Data on reasons for leaving the study will also be collected. A demographic form will be used to collect basic demographics including age, education, sex, marital status, income, and individuals’ provincial health insurance number. The provincial health insurance number will be used for data linkage to provincial administrative health care databases in order to conduct the economic evaluation.

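### The repeated measures ANOVA for the continuous secondary outcomes leaves the role of baseline open and names no baseline adjustment; each natural reading has less power than a baseline-adjusted analysis, and one shrinks the estimate by a third

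*Protocol article*

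**What the plan says.** The third aim in Study Design is to test whether the "intervention will improve the quality of life for clients and family/friend caregivers". The corresponding secondary outcomes are listed there as "2) client functional status and quality of life in the home, (3) family/friend caregiver stress, and (4) family/friend caregiver functional health status".

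Under Phase I: Survey Data Collection, researchers meet clients and caregivers "in the home of the client or by phone at baseline, 6 months, and 12 months to collect data". Recruitment fixes the order: "research staff will collect baseline data before initiating random allocation into control and intervention groups".

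The analysis is given in Quantitative Data. The paragraph opens with "Quantitative data will be analyzed at baseline, with subsequent analysis of primary/secondary outcomes at 6 months and 12 months". The method for continuous outcomes follows: "Repeated measures analysis of variance will measure mean differences between groups on continuous variables". No term of the ANOVA is named, baseline is given no explicit role in it, and no covariate is mentioned for these outcomes. For the cost outcome, by contrast, Economic Analysis does state a regression with adjustment.

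**The concern.** Aim 3 concerns a difference between arms after randomization. Baseline is measured before allocation and cannot carry a treatment effect. It is useful as a covariate and harmful if averaged into the outcome.

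The stated sentence allows three analyses:

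- **A.** Three visits as levels, group main effect tested. This compares each person's average over all three visits, so a third of the averaged score carries no effect.
- **B.** Three visits as levels, group-by-time tested. There is no dilution, but it is a 2-df test of any difference in profile and gives no single treatment effect.
- **C.** Only 6 and 12 months as levels, group main effect tested. There is no dilution, but the baseline score goes unused.

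At stake is the sensitivity of the quality-of-life and caregiver results. Under A, a real benefit would also be reported one third too small.

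**Working it through.** **The plan's own figure.** Sample Size Calculation gives no power for continuous outcomes. Its only figure is for institutionalization, starting from "the total institutionalization proportion among controls being equal to 0.41" against 0.27, with 80% power, alpha .05, 2:1 allocation and 10% dropout. The continuity-corrected two-proportion formula (two-sided) gives 146 + 292. Dividing by 0.9 gives 163 + 326 = 489, and multiplying by 1.10 gives 161 + 322 = 483. Both are within 3% of the stated 480, so the figure reproduces. It has no bearing on the continuous outcomes except to fix the numbers available.

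**Inputs.**

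- From the article: 160 intervention and 320 control; less 10%, 144 and 288. Three visits, baseline before allocation.
- Assumed, because the article does not give them: SD 1 at each visit; equal between-visit correlation ρ of 0.4, 0.6 or 0.8; constant effect d = 0.25 SD at 6 and 12 months; complete data; two-sided 5% test.

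k = 1/144 + 1/288 = 0.010417.

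**Dilution under A.** The expected baseline difference is 0 by randomization, so the main effect is (0 + d6 + d12)/3 = (2/3) × (d6 + d12)/2. The estimate is two thirds of the average post-baseline effect. Simulation (4,000 runs per setting) gave ratios of 0.66 (ρ 0.5) and 0.68 (ρ 0.7).

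**Validity under A.** The same expression is zero exactly when the average 6/12-month effect is zero. Simulated type I error was 4.8% (ρ 0.5) and 5.2% (ρ 0.7).

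**Power formulas.**

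- A: mean 2d/3, variance k(1 + 2ρ)/3.
- B: noncentral F on 2 and 860 df, λ = (2/3)d²/[(1 − ρ)k].
- C: mean d, variance k(1 + ρ)/2.
- Baseline-adjusted 6/12-month mean: mean d, variance k[(1 + ρ)/2 − ρ²].

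**Worked at ρ = 0.6, d = 0.25.**

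- A: 0.1667/√0.007639 = 0.1667/0.0874 = 1.91, power 48%.
- B: λ = 0.041667/(0.4 × 0.010417) = 10.0, power 81%.
- C: 0.25/√0.008333 = 0.25/0.0913 = 2.74, power 78%.
- Adjusted: 0.25/√(0.010417 × 0.44) = 0.25/0.0677 = 3.69, power 96%.

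| Analysis | ρ = 0.4 | ρ = 0.6 | ρ = 0.8 |
|---|---|---|---|
| A. Three-visit group effect | 56% | 48% | 42% |
| B. Group-by-time, 2 df | 63% | 81% | 98% |
| C. Unadjusted 6/12-month mean | 83% | 78% | 73% |
| Baseline-adjusted 6/12-month mean | 91% | 96% | >99% |

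At 0.20 SD and ρ 0.6 the four figures are 33%, 61%, 59% and 84%.

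**Sensitivity to ρ.** Set the effect so that the adjusted analysis has 80% power. Under equal correlation / AR(1) correlation, A then has 63%/63% at ρ 0, 48%/55% at 0.3, 37%/46% at 0.5, 30%/40% at 0.6, 24%/33% at 0.7, 17%/24% at 0.8 and 11%/15% at 0.9. The relative loss therefore runs from about a fifth to over four fifths. If instead C is set at 80% power, A has 47% to 63%.

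**The case against.** The strongest reply is that the article does not commit to analysis A. It neither makes baseline a level of the repeated factor nor names the main effect, and the paragraph's opening sentence sets baseline apart from the outcome analyses at 6 and 12 months. Analysis C fits that text, and B is a standard choice for data of this kind. This stands: the one-third shrinkage is conditional on one plausible reading.

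A second reply is that a condensed article may leave the model term and covariates to the full protocol or analysis plan. That is fair as to missing detail. But the article does name a method and what it is to measure, and it reports adjustment where it plans it, for costs. The point is that the stated method is improvable under each of its readings.

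Third, the advantage depends on the pattern of effect. If the effect appeared only at 12 months (0.25 SD, ρ 0.6), B keeps λ = 10.0 and 81% power. The adjusted 6/12-month average would see 0.125/0.0677 = 1.85, about 45%. The adjusted 12-month difference would see 0.25/√[0.010417 × (1 − 0.36)] = 0.25/0.0816 = 3.06, about 86%. So the choice of contrast matters, and the 12-month difference should be reported too.

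Two stronger readings are tempting, and neither is supported:

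- *Analysis A tests a different null from no treatment effect.* Under randomization it does not, as shown above.
- *Chance baseline imbalance makes A invalid.* In a null simulation at ρ 0.6, A rejected in 48% of trials with a baseline gap of at least 0.2 SD, against 4% with adjustment. Those were 5.2% of trials, and 5.2% × 48% = 2.5% of all trials, which already sits inside the nominal 5%. It illustrates why adjustment helps; it is not an additional error.

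**Conclusion.** The point holds as one of efficiency and clarity. The stated method does not fix the role of baseline or the term tested, and it names no adjustment for a score the trial already collects. With a constant effect of 0.25 SD, the shortfall against the adjusted analysis at ρ 0.6 is 48 points for A, 15 for B and 18 for C. At ρ 0.8 the shortfall for B almost vanishes, and at ρ 0 adjustment gains nothing over C. Only under A is the estimate diluted, to two thirds.

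A reader might infer that the plan loses half its power. That needs reading A, a mid-range correlation that the article does not give, and the adjusted analysis as comparator, so it should not be stated as a property of the plan. The affected outcomes are all secondary. The primary outcome and the target of 480 are untouched.

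**What to change.** Replace the ANOVA sentence in Quantitative Data with wording such as: *For each continuous outcome with a baseline value, the 6- and 12-month scores will be analysed in a linear mixed model with arm, visit, arm-by-visit interaction and the baseline score of the same measure as covariate. Baseline is not an outcome time point. The test is the average of the 6- and 12-month differences between arms; the 12-month difference is also reported.*

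The cost is one sentence. No new data or participants are needed, because baseline scores are already collected before allocation. The sponsor should confirm the average as the test before outcome data are seen; if the effect is expected mainly at 12 months, this is the time to consider that. The article does not say which measures lack a baseline value, so the sentence is limited to those that have one.

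### Repeated measures ANOVA keeps only participants with all three visits; if admission ends interviews, loss would be about 47% of controls versus 34% of the intervention arm and could bias client quality of life

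*Protocol article*

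**What the plan says.** The Quantitative Data section fixes the method for continuous outcomes: "Repeated measures analysis of variance will measure mean differences between groups on continuous variables". It names no other model for them. Software is mentioned only in connection with the descriptive summaries: "Using SPSS Statistics version 25 (IBM Corp) statistical software, descriptive statistics will provide a profile of study participants".

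Under Phase I: Survey Data Collection, researchers meet clients and caregivers "in the home of the client or by phone at baseline, 6 months, and 12 months to collect data". Reasons for leaving the study are recorded. No rule there, or elsewhere in the article, says whether a client's admission to long-term care ends that client's or the caregiver's interviews.

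The Sample Size Calculation section assumes "the total institutionalization proportion among controls being equal to 0.41 and the proportion or the experimental subjects at 0.27", and separately "a 10% dropout and/or lost to follow-up rate". The loss figure is not split by arm. The targets are "160 participants for the intervention group and 320 for the control group".

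Under Study Design, client quality of life is a secondary outcome defined for the home setting, and improving quality of life for clients and caregivers is one of the three primary aims.

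**The concern.** Classical repeated measures ANOVA is a complete-case method: a participant missing one of three visits contributes nothing to it. The trial enrols people judged likely to enter long-term care within 12 months, which is also the survey window. Admission is therefore an obvious route to a missed interview, and the sample size assumptions make admission more common among controls.

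If frailer clients are both more likely to be admitted and lower on quality of life or function, the remaining controls would be selected more strongly for good scores than the remaining intervention clients. A programme that succeeded in keeping frail people at home could then look worse on quality of life because it did so. The outcomes behind the quality-of-life aim would be compared between unlike subsets, and 6-month scores of clients lost later would drop out of this analysis.

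**Working it through.** **1. The plan's own figure.** Inputs from Sample Size Calculation: 0.27 versus 0.41, 80% power, alpha 0.05 (two-sided assumed), two controls per intervention client, 10% loss. The pooled proportion is (0.27 + 2×0.41)/3 = 0.363. Without continuity correction the intervention arm needs 136; with it, 146. Allowing for 10% loss, 146/0.9 gives 163 and 146×1.1 gives 161. The stated 160 and 320 are therefore reproduced closely, and the rates can be taken as the plan's working assumptions.

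**2. Loss from the ANOVA.** Let f be the share of admissions that cost a visit (not given in the article, so varied from 0 to 1), p the event rate, and let the 10% dropout be independent. Loss = 1 − (1 − f×p)×0.9. The rates carry no time horizon; 12 months is assumed.

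| f | Control (p = 0.41) | Intervention (p = 0.27) | Gap |
|---|---|---|---|
| 1 | 1 − 0.59×0.9 = 46.9% | 1 − 0.73×0.9 = 34.3% | 12.6 points |
| 0.5 | 1 − 0.795×0.9 = 28.5% | 1 − 0.865×0.9 = 22.2% | 6.3 points |
| 0 | 10% | 10% | 0 |

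At f = 1 the complete cases are 0.531×320 = 170 controls and 0.657×160 = 105 intervention clients. That is 275 of 480, so 205 (43%) are excluded.

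**3. Bias in a 12-month score, by formula.** Assume no true effect, a standardized outcome (higher is better) and correlation of size ρ between poor score and admission risk (ρ is an assumption). With the top fraction p of risk lost, the mean among those kept rises by ρ×φ(z)/(1 − p). The multipliers are 0.453 for p = 0.27 and 0.659 for p = 0.41, a difference of −0.206.
- ρ = 0.3: 0.3×(−0.206) = −0.062 SD
- ρ = 0.5: 0.5×(−0.206) = −0.103 SD

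At f = 0.5, with the lost half of admissions taken at random, the multipliers become 0.5×0.331/0.865 = 0.191 and 0.5×0.389/0.795 = 0.245. The difference is −0.053, which gives −0.016 SD (ρ = 0.3) and −0.027 SD (ρ = 0.5). The bias falls to about a quarter.

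**4. Bias in the ANOVA contrasts, by simulation.** Large samples, no true effect, visit correlations 0.5 to 0.6, f = 1, correlation 0.6 between the score and the loss process. Sizes in SD; nonzero values work against the intervention.

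| Loss depends on | Group effect over visits | 12-month difference | Group-by-time | Likelihood-based model, 12 months |
|---|---|---|---|---|
| Nothing related to outcome | 0 | 0 | about 0 | 0 |
| Observed 6-month score | 0.09 | 0.07 | about 0 | about 0 |
| Unseen 12-month score | 0.09 | 0.13 | 0.06 | 0.09 |

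With equal event rates (41% in both arms), every entry is about zero.

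**The case against.** The strongest reply is that the key premise is not in the article. The figures 0.41 and 0.27 are rates of the primary event, not of missed interviews, and the only stated loss is a flat 10%. Phone interviews are allowed, and no rule stops follow-up at admission. A reader might infer that the plan's own rates show loss differing by arm. They do not: that needs admissions to cost visits, and the 27% itself needs the intervention to work as assumed. This stands, and the finding is conditional for that reason.

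Other tempting readings also go too far:
- **That bias is certain.** Unequal loss alone produced none; the loss must also be related to the outcome.
- **That caregiver burden is equally affected.** Caregivers are separate respondents and are not themselves admitted. Nothing in the article ties a client's admission to loss of the caregiver's interview.
- **That the plan expects deaths to add to the loss.** It never mentions them; the terminal hospital admission it counts is one spent awaiting long-term care.
- **That the 12-month bias gives the false-positive rate of the planned test.** A two-sample error calculation at 12 months is not the ANOVA group or group-by-time test, and the latter was unbiased in one informative scenario.

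It can also be said that missing-data handling belongs in a fuller document, and that the article plans analyses at 6 as well as 12 months. Silence on missing data is indeed no fault here. The objection is to the method that the article does name.

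**Conclusion.** The point holds in conditional form, with medium confidence. The only method named for the continuous outcomes is, in its classical form, a complete-case analysis, and the trial population makes loss through admission plausible.

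If every admission costs a visit and the loss is related to the outcome, client quality of life and functional status could be biased by roughly 0.06 to 0.13 SD against the intervention. If only half cost a visit, the formula gives about 0.02 to 0.03 SD. Bias is about zero if admissions cost no visits, if loss is unrelated to the outcome, or if event rates are equal. For caregiver burden the same mechanism is possible but has less support.

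The result rests on assumed correlations, a 12-month horizon for the event rates, and independent 10% dropout. Even if no bias arises, the named analysis discards observed visits that a better method would use.

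**What to change.** Replace repeated measures ANOVA with a linear mixed model for the 6- and 12-month scores: arm, time, arm-by-time and province as fixed effects, baseline score as covariate, unstructured covariance, and all randomized participants with any follow-up.

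Then make three additions:
- State that client and caregiver interviews continue by phone after admission; the survey section already permits phone contact.
- State how client quality of life, defined for the home setting, is to be interpreted once a client has been admitted. Otherwise post-admission scores change what is being estimated.
- Add one sensitivity analysis for loss related to institutionalization.

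The cost is slightly more analysis work and some extra phone interviews. SPSS 25, already named, fits the model. The Results section puts the end of primary-outcome data collection in winter 2020, so extra interviews can help only dyads still in follow-up; the model can be changed at any time before analysis.

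The mixed model is not a full cure. It removed the bias when loss depended on the observed 6-month score, but left 0.09 of 0.13 SD when loss depended on the unseen 12-month score. That is why continued interviews and the sensitivity analysis are needed as well.
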